#### Feasibility of the study and structure of exposomic data

2.4.2

Due to the high number of variables selected for EXPOSITION, we tested the information content of the variables for each exposomic component and their integration with correlated variables. Factor analysis was performed using a hybrid dataset (real data already collected by the researchers and synthetic data modeled on the real dataset), to explore how different exposures may cluster into common latent factors, whether the data may show sufficient correlation/structure to be meaningfully summarized, and how dimensionality can be reduced while preserving relevant information. The analysis performed on synthetic data indicated that the selected variables of the external exposome can cluster into 5 latent factors, which appear biologically and clinically plausible in the context of Multiple Sclerosis. These findings support the creation of exposure indices for subsequent informative analyses in the real dataset. To illustrate the analytical framework, we provide additional details in the Supplementary materials.

#### Data pre-processing, integration and missing imputation

2.4.3

Social, demographic, clinical, internal and external exposome individual data from the sample of pwMS relevant to research objectives, in line with local and European regulatory requirements, will be stored within a unified EXPOSITION database and linked using the individual pseudonymized code created for each pwMS. Air pollution and urbanisation data will also be linked. Specifically, pwMS will be assigned the ecological characteristics (e.g., pollution gridded emission) of the geographic unit (municipality) where they are residents. Candidate and validated biomarker’s distribution will be evaluated. Variables with skewed distributions will be transformed (e.g., log-transformation) as appropriate. Values below the limit of detection (LOD) will be handled using standard procedures (e.g., substitution with LOD/√2) or multiple imputation, depending on the proportion of censored values. Missing values will be addressed using multiple imputations under the missing-at-random assumption, generating several imputed datasets that will be analysed separately and combined using Rubin’s rules.

All the analyses will be performed with the R statistical software, using the most up-to-date packages and pipelines. We will use Bioconductor, R’s development project, for the analysis and interpretation of high-throughput genomic data, which currently comprises more than 900 interoperable packages.

#### Data description

2.4.4

The first round of statistical analyses will be used to describe the pwMS sample and internal and external exposome. Descriptive statistics will be performed with mean, standard deviation, median and interquartile range, or frequencies depending on the nature of the variables. Graphical descriptions will be used by boxplots or violin plots, with the option of grouping with the categorical exposures.

#### Exposome clustering, correlation and association analyses

2.4.5

a) *Clustering.* Clusters of individuals who share similar exposure patterns will be identified using hierarchical clustering.b) *PCA.* Principal component analysis will be used to reduce the dimensionality of the exposome (e.g., PCA standard, robust or FAMD for both categorical and continuous exposures).c) *Assess correlation structure.* Pearson, Spearman or Cramer coefficients, as appropriate, will be calculated to determine correlation structures between variables of the same exposome component. A correlation matrix and heatmap or Circos plot will be created.d) *Validated biomarkers’ behaviour in the pwMS sample (Neurofilament proteins, levels of pro- and anti-inflammatory cytokines, vitamin D level).* They will be tested for correlation with the miRNA relative expression and with alpha, beta diversity and relative abundances; they will also be tested for association with each exposure variable of the external exposome.e) *Single exposure association analysis with the primary endpoint.* To estimate the association between the external exposome and the expression of miRNAs (the primary endpoint), separate regression models (negative binomial, linear, or mixed-effects, depending on the outcome distribution) will be fitted, taking account of previous clustering, and adjusting for confounders and other modifiers of effect (including the validated biomarkers described above).f) *Single exposure association analysis with the secondary endpoints.* Gut and nasal microbiota data, as the secondary endpoint, will be analysed employing non-parametric statistical tests (e.g., Mann–Whitney, Kruskal-Wallis tests) for comparing alpha-diversity and relative abundances, whereas a permutational multivariate analysis of variance with F-ratios (“adonis”) will be used for beta-diversity comparison. Linear regression models will be employed to perform multivariate statistics on biodiversity and relative abundances, correcting estimates for confounders and modifiers of effect (including DMT type and dietary habits as MEDI-LITE and DII).g) *Apply multiple testing correction.* For each association tested, both raw *p*-values and FDR (Benjamini–Hochberg) q-values will be reported; if exposures are strongly correlated, the ENT-Bonferroni p-value will also be reported (59–61)h) *Variable selection (e.g., exposures).* The modelling procedure will identify a final set of predictors of miRNAs or microbiome variation, allowing for the simultaneous inclusion of multiple exposures within the same model. Variable selection will be performed using generalised multivariable linear models estimated via penalised maximum likelihood, applying either a lasso or elastic net penalty to determine the most informative exposures associated with the outcomes.

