**Figure 1 fig1:**
[figure not shown]
External exposome and biological responses in multiple sclerosis: the EXPOSITION approach. The diagram depicts the urban exposome domains hypothesized to influence MS. The External Exposome (beige arc) summarises the broad environmental context including urbanization and air quality typical of Po Valley settings. The External Specific Exposome (green arc) represents individual-level lifestyle and behavioural factors, including smoking habits, quality of life, dietary supplement use, physical activity, and nutrition. The Internal Exposome (blue arc) comprises measurable biological mediators and effect markers, including gut microbiota, neurofilament, circulating cytokines, and microRNA. Bidirectional arrows indicate dynamic interactions across domains, converging on MS pathophysiology (central illustration).

Particularly, the primary objective of the EXPOSITION study is to investigate the variation of microRNA (miRNA) expression, in response to general external exposome (urban air pollution and urbanization), as well as occupational and lifestyle external exposome components in pwMS, controlling for other validated biomarkers (e.g., serum pro- and anti-inflammatory cytokine levels, serum neurofilaments levels, serum vitamin D levels), gender, age, anthropometric measurements, and medical history.

The secondary objective is to investigate the variation of the gut and nasal microbiota composition as candidate biological biomarkers of OS and inflammation, in response to the exposome components and other variables included in the primary objective methodological framework. The microbial profiles will be evaluated in terms of (i). Biodiversity (alpha-diversity), estimating the number of taxa in each sample and statistically comparing estimates across the experimental groups; (ii). Composition (beta-diversity), evaluating the pairwise similarity among the samples and clustering them according to their distances; (iii). Bacterial groups (relative abundances), evaluating whether a bacterial taxon is significantly increased or depleted in pwMS belonging to the different exposome profiles under investigation.

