### Population, inclusion criteria and informed consent

2.2

To address EXPOSITION’s purposes 200 persons with MS attending the Multiple Sclerosis Center of the IRCCS Mondino Foundation, Pavia (Italy) have been selected and recruitment is under way for this study, according to the following inclusion criteria: age ≥18 years; diagnosis of MS according to 2017 McDonald criteria (26); relapsing–remitting (RR) MS, which is the most common MS type and is characterized by alterations of relapses and remission periods (7); routine clinical examinations scheduled in the study period March–April, 2024 and October–April, 2025; Residence in the provinces of Pavia or Milan (Italy); informed consent form signed. Particularly, the study will be conducted in Pavia and Milan, the Northern Italy nodes of the National Biodiversity Future Center (NBFC) (27), which is an Italian research consortium integrating universities, institutes, and stakeholders to study, monitor, and restore biodiversity and to translate evidence into policies, technologies, and nature-based solutions for human and ecosystem health. Thus, Milan represents a large metropolitan and industrial hub with high traffic density, complex socio-economic gradients, and sustained environmental pressures, while Pavia is a medium-sized university city with peri-urban and agricultural interfaces and substantial daily commuting flows to Milan. This paired selection will capture heterogeneous but complementary northern urban exposome profiles within a shared atmospheric basin typical of the Po Valley and characterized by frequent stagnation events.

People refusing to participate in the study will be excluded. Potentially eligible pwMS will be screened by a neurologist, an expert in MS, who will verify that all the inclusion criteria will be fulfilled.

Participants will be selected from the Pavia Database of Multiple Sclerosis of the Multiple Sclerosis Center of the IRCCS Mondino Foundation, Pavia (Italy). It includes 1,400 MS patients, has been active since 1990 and has been part of the ‘Italian Multiple Sclerosis Register’ since 2015.

The study will follow the Declaration of Helsinki. Written informed consent will be obtained from the participants.

Ethical approval was granted by the Ethical Committee of IRCCS Policlinico San Matteo (Pavia) (protocol number: 0040023/23; Accepted: 25/07/2023). The EXPOSITION protocol has been registered on www.clinicaltrials.gov (NCT06325358).

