##### Urbanization

2.3.2.2

The European degree of urbanisation classification (28) based on 2020 census results will be adopted to stratify territories according to urbanisation. Municipalities in the provinces of Pavia and Milan will be classified as cities, town-suburbs or rural areas.

The municipalities classifiable as cities by DEGURBA (28) will be only Pavia in its province, Milano and 47 other territories in the Milan province. Moreover, the territories classifiable as town-suburbs will be 27 in Pavia and 77 in Milano. Pavia province will have 158, and Milano 8 rural areas. DEGURBA uses country-specific definitions of what a city is. In Italy, according to the ISTAT definition, a city (or urban area) is defined as a local administrative unit with a minimum of 50,000 inhabitants, where most of the population lives in a high-density cluster.

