##### Occupational factors

2.3.2.5

The potential exposure to harmful agents in the workplace will be assessed through a specific questionnaire aimed at identifying the exposure to the entire working life of the subjects involved. The information collected regarding the duration of each work activity and the tasks performed throughout work life will be investigated. This will include the specific sector(s) of employment, the main tasks performed, and the workplace location(s). Following this information, the related International Standard Classification of Occupation (ISCO) code will be assigned (40). The ISCO code will be adopted to determine the level of occupational risk for SM of the involved subjects, according to four classes: (1) work activities associated with specific occupational risks connected with SM (such as agricultural workers, offshore workers, and hairdressers (41); (2) work activities associated with occupational risks less likely connected with the SM diagnosis (such as exposure to toxic oil well fumes, low-frequency magnetic fields, and pesticides (41); (3) work activities not directly connected with increased risk for SM, but identified as potential causes of relevant professional diseases through inflammatory pathways (e.g., exposure to carcinogenic and mutagenic agents, toxicants, ionizing radiation, etc.); (4) work activities not associated with specific relevant occupational diseases (e.g., office workers, trade workers, unemployed). In the case of multiple activities during working life, the prevalent exposure, namely the one correlated with the longest working period of the subject, will be considered.

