##### Gut and nasal microbiota analysis (secondary endpoints)

2.3.3.2

The stool and nasal samples will be stored at −80 °C until genomic DNA extraction. The Maxwell® RSC Faecal Microbiome DNA Kit and Maxwell® RSC Pathogen Total Nucleic Acid Kit will be employed for DNA isolation from stool and nasal samples, respectively, using a Maxwell RSC automated extractor (Promega s.r.l., Milan, Italy), according to the manufacturer’s recommendations. The quality and quantity of gDNA will be assessed by TapeStation 4,200 system (Agilent, Santa Clara, CA, USA) and Qubit 4 fluorometer (Invitrogen, Waltham, MA, USA). Afterwards, the sequencing libraries will be prepared by using the MICROLAB STARlet NGS UV automated liquid handling station (Hamilton Italia Srl, Agrate Brianza, Italy), following an NGS metabarcoding approach. The 16S Metagenomic Sequencing Library Preparation protocol will be employed for the amplification of the V3-V4 hypervariable regions of the 16S rRNA gene and indexing by dual Nextera® XT indexes (Illumina, San Diego, CA, USA). All libraries, quantified by the Qubit 4 fluorometer and pooled at equimolar concentrations, will subsequently be sequenced using the Illumina NextSeq1000 platform through a 2x300bp paired-end run.

Raw sequencing reads will be processed following a specific pipeline, involving the merging of two paired reads overlapping, generating a single fragment covering the whole V3-V4 regions, the trimming and filtering of low-quality reads and the grouping to Amplicon Sequence Variants (ASVs) by the DADA2 denoising pipeline (50). Taxonomic classification will be performed by the RDP classifier (51) against the latest release of the SILVA reference database (52).

Biodiversity will be estimated by calculating the alpha-diversity for each sample using different metrics, such as Shannon’s entropy index, observed species, Chao1 index and Faith’s phylogenetic diversity index. Pairwise similarity between microbial profiles will be assessed using the unweighted and weighted implementations of the UniFrac distance (53). Microbial composition will be expressed as the relative abundance of taxa at different levels, from phylum to genus. Due to the lower complexity of the nasal microbiota, its composition will be characterised down to the species level for some of the most abundant genera (e.g., *Corynebacterium, Moraxella, Haemophilus*).

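### For categorical exposures, pair the adonis beta-diversity test with a dispersion check and a Welch-type statistic, so that a difference in scatter is not reported as a difference in composition

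*Protocol article*

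**What the plan says.** - **Test.** Section 2.4.5(f) of the protocol article says that "a permutational multivariate analysis of variance with F-ratios (“adonis”) will be used for beta-diversity comparison". It names no other test for beta-diversity.
- **Distance.** Section 2.3.3.2 specifies the "unweighted and weighted implementations of the UniFrac distance".
- **Meaning given to the outcome.** The secondary objective in 2.1 lists "Composition (beta-diversity), evaluating the pairwise similarity among the samples and clustering them according to their distances".
- **Categorical exposures.** In 2.3.2.2, municipalities "will be classified as cities, town-suburbs or rural areas". In 2.3.2.5, the job code serves to "determine the level of occupational risk for SM of the involved subjects, according to four classes". Smoking has three categories (2.3.2.3), and hierarchical clustering produces data-driven exposure groups (2.4.5(a)). No number of participants per category is given for any of these.
- **Multiplicity.** Under 2.4.5(g), raw p-values and "FDR (Benjamini–Hochberg) q-values will be reported".
- **Other evidence on the microbiota.** 2.4.5(f) also tests relative abundances directly and fits adjusted linear regressions to biodiversity and abundances.

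**The concern.** Adonis shuffles people across exposure groups and compares between-group variation with a pooled within-group term. The null that this generates is full exchangeability: same centroid and same spread. The stated question is narrower, namely whether composition varies with exposure.

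The two questions come apart when groups differ in both size and spread. If the smaller group is the more scattered, the pooled term understates the noise in its centroid and the test over-rejects. If the larger group is the more scattered, the test becomes conservative and loses power. This happens with no confounder present, so covariate adjustment does not remove it. False-discovery control does not remove it either, because it takes the same p-values as input.

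The groups are observed rather than allocated, so nothing in the design keeps their sizes similar. At stake is how one of the three microbiota readouts in the secondary objective is interpreted: a scatter difference could be reported as a shift in the community, or a real shift could go unreported.

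**Working it through.** **Inputs from the article.** Section 2.4.1 gives 168 evaluable participants, 15% dropout and 200 recruited. These agree: 168/0.85 = 197.6, so 198, rounded up to 200; and 200 × 0.85 = 170. They were derived for the miRNA endpoint. No power or sample size is stated for beta-diversity, so there is no figure for this test to reproduce; 168 and 170 serve only as realistic totals.

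**Assumed inputs.** Level 0.05, the group sizes, the spread ratios, and Euclidean data in place of UniFrac.

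**Step 1: direction, by algebra.** With k groups of size n_i, total N, identical centroids and per-axis SD σ_i:

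- E[between mean square] = Σ(1 − n_i/N)σ_i² / (k − 1)
- E[within mean square] = Σ(n_i − 1)σ_i² / (N − k)

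Shuffling labels mixes the groups, so the permutation distribution is centred near a ratio of 1. The observed ratio is centred as follows.

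- **84/56/28, SDs 1/1.25/1.5 (smallest group most scattered).** Between: (0.5×1 + 0.667×1.5625 + 0.833×2.25)/2 = 1.708. Within: (83×1 + 55×1.5625 + 27×2.25)/165 = 1.392. Ratio 1.23, so too many rejections.
- **84/56/28, SDs 1.5/1.25/1 (largest group most scattered).** Between: (0.5×2.25 + 0.667×1.5625 + 0.833×1)/2 = 1.500. Within: (83×2.25 + 55×1.5625 + 27×1)/165 = 1.816. Ratio 0.83, so too few.
- **56/56/56, SDs 1/1.25/1.5.** Between: 0.667×4.8125/2 = 1.604. Within: 55×4.8125/165 = 1.604. Ratio 1.00.
- **Equal spreads, any sizes.** Ratio 1.00.

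Both imbalances are therefore needed.

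**Step 2: size, by simulation.** Ten-dimensional Euclidean data, N = 168, permutation p-values. Wd* is the Welch-type distance statistic, which weights each group by n_i/s_i² instead of pooling the spread. Rejection with identical centroids at nominal 5%:

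| Setting (SD ratio 1.5 where unequal) | adonis F | Wd* |
|---|---|---|
| 84/56/28, smallest group most scattered | 17–19% | 4–5% |
| 84/56/28, largest group most scattered | 0–2% | 5% |
| 120/48, smaller group more scattered | 19–26% | 5–7% |

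With equal spreads adonis holds its level. With equal group sizes its rejection stays at 4–8%. The ranges span separate runs; with 300 replicates the Monte Carlo standard error at 18% is √(0.18×0.82/300) = 2.2 points.

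A separate two-group run (N = 170, 20 dimensions, 1,000 replicates) shows how far the size depends on the assumptions. With the smaller group more scattered at SD ratios 1.25/1.5/2, rejection was 15/29/49% at 51:119 and 25/49/76% at 34:136. With the larger group more scattered it was 1.1% or less. At 85:85 with unequal spreads it was 3.8–5.0%, and with equal spreads 3.5–5.1% at every split.

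**Step 3: power.** True shift of 1 SD on one axis in the smallest group, 84/56/28:

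| Spread | adonis F | Wd* |
|---|---|---|
| Equal | 83–84% | 83–84% |
| Larger groups more scattered, ratio 1.5 | 37–40% | 74–76% |
| Smaller groups more scattered, ratio 1.5 | 75–76% (inflated level) | 47–49% |

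In the middle row Wd* also falls, from about 84% to about 75%. That part of the loss is added noise and should not be charged to adonis.

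**The case against.** The strongest objection is that adonis is a standard test for UniFrac distances and that nothing in the article states it wrongly or contradicts it. A companion dispersion check is the kind of detail a journal article leaves to a full protocol or analysis plan, and neither is shown. This stands: the missing check cannot be counted as a fault. A reader might infer that the plan is wrong as written, and the document does not support that. What remains is a suggestion about a statistic that the article does name and an outcome that it does label.

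Four further objections also stand, in part or in full.

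- **Harm is conditional.** No passage gives group sizes, or suggests that spread differs by urbanisation, smoking or occupation. A reader might take the inflated rates as a forecast for this study; they are not.
- **Reach is limited.** Pollutant concentrations, dietary scores, MET-minutes and sleep scores are numeric. The group-size argument reaches them only if they are categorised, so it would be wrong to say that beta-diversity results are compromised across the whole exposome.
- **The intended reading is partly inferred.** The objective speaks of pairwise similarity and clustering by distance, and a difference in scatter is a difference in pairwise similarity. Still, the label is composition, and the article gives no rule for telling the two apart.
- **The simulations are not UniFrac.** In a compositional metric, changing the spread may itself move the centroid, so the separation is less clean than in the Euclidean case.

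The abundance tests and adjusted regressions limit the consequence but do not change what the adonis p-value means.

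**Conclusion.** This is a worthwhile, inexpensive improvement to a secondary analysis, not a demonstrated error. It applies to categorical exposures only: urbanisation, smoking, occupational class and hierarchical clusters. If such groups differ in both size and spread, the pooled F-ratio does not isolate composition. At 84/56/28 and an SD ratio of 1.5, false rejection moves from 5% to about 17–19% in one direction and about 0–2% in the other. The direction follows from the algebra; the size rests on assumed group sizes, spread ratios, dimension and Euclidean distances. It would not be right to conclude that adonis should be dropped: Wd* takes neither covariates nor continuous exposures, and it has less power when the smaller group is the more scattered one.

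**What to change.** Keep adonis. In 2.4.5(f), or in the analysis plan, add that for each categorical exposure the team will also report:

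1. a test of multivariate dispersion (PERMDISP, betadisper in R) on the same UniFrac distances; and
2. the Welch-type statistic Wd* with a permutation p-value.

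Call the result a composition (location) difference only if dispersion is homogeneous or Wd* agrees. Otherwise report that location and dispersion cannot be separated. Group sizes should be shown beside each result. If an unpublished analysis plan already contains this, confirming it is enough.

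**Cost.** A sentence or two of text and a few lines of code on distance matrices already planned; no new data. Nothing is lost at equal spread (83–84% power for both statistics). The real price is fewer composition claims when the smaller group is the more scattered: about 47–49% power for Wd* against 75–76% for adonis, part of which is the inflated level.

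### Section 2.4.5 f specifies confounder correction for alpha-diversity and relative abundances but names no covariates for the adonis test of beta-diversity, so a treatment-driven difference in composition could be read as an exposome effect.

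*Protocol article*

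**What the plan says.** Section 2.1 (Objectives) sets the secondary objective and defines its terms. The first outcome is "Biodiversity (alpha-diversity), estimating the number of taxa in each sample and statistically comparing estimates across the experimental groups". The second is "Composition (beta-diversity), evaluating the pairwise similarity among the samples and clustering them according to their distances". The third is the relative abundance of bacterial groups. The same paragraph says these will be studied together with the further variables of the primary framework, which controls for gender, age, anthropometry and medical history among others.

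Section 2.4.5 f assigns the methods in two steps.

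- Group comparisons: "non-parametric statistical tests (e.g., Mann–Whitney, Kruskal-Wallis tests) for comparing alpha-diversity and relative abundances". Composition is handled separately, by a permutation test on the distances (adonis), which "will be used for beta-diversity comparison".
- Adjusted models: "Linear regression models will be employed to perform multivariate statistics on biodiversity and relative abundances, correcting estimates for confounders and modifiers of effect", with the covariates described as "including DMT type and dietary habits as MEDI-LITE and DII".

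Beta-diversity is measured by unweighted and weighted UniFrac distance (section 2.3.3.2). DMT history and current treatment are collected (section 2.3.1).

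**The concern.** By the article's own definitions, biodiversity means alpha-diversity and composition means beta-diversity. The adjusted step therefore covers two of the three outcomes, and composition is the one with no adjusted analysis assigned to it. The article does more here than stay silent on adjustment: it names covariates for the secondary endpoints and lists the outcomes they apply to, and beta-diversity is not on that list.

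The study is cross-sectional and observational, and the inclusion criteria do not restrict treatment. The plan treats DMT type as something to correct for when the microbiota is the outcome. If DMT type shifts the community and is unevenly spread over an exposure (degree of urbanisation, for example), a one-factor adonis credits part of the treatment difference to that exposure. The Discussion means the findings to point to modifiable factors and to inform policy, so a composition result that cannot be separated from treatment would be of limited use.

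**Working it through.** **Plan's own figure.** No figure is given for beta-diversity. The only sample size is for a single-miRNA comparison: 168 evaluable with 15% dropout. 168 / (1 − 0.15) = 197.6, so 198, which agrees with the stated 200. 200 × 0.85 = 170 was used as n below. It is borrowed, since the 15% refers to blood sampling and not to stool or nasal samples.

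**Text check.**

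| Outcome (2.1) | Comparison in 2.4.5 f | Adjusted analysis in 2.4.5 f |
|---|---|---|
| Alpha-diversity | Rank tests | Linear regression with DMT type, MEDI-LITE, DII |
| Relative abundances | Rank tests | Linear regression with DMT type, MEDI-LITE, DII |
| Composition (beta) | adonis | None named |

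**Simulation of the mechanism.** All inputs other than n are assumptions, not figures from the article. The exposure is binary, split 50/50, and has no effect. DMT is binary, with its prevalence set separately in each exposure group. The community has 60 independent dimensions with unit noise and Euclidean distance. There were 300 data sets with 199 permutations each, tested at 5%. The DMT effect per dimension is b = √[R² / (1 − R²) / 0.25]. It adds variance 0.25·b² = R² / (1 − R²) to noise of 1, so DMT's share of the total is R². The adjusted model enters DMT before the exposure, so the exposure is tested by its marginal term.

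| DMT prevalence, exposed vs unexposed | DMT share R² | Rejection without DMT | Rejection with DMT |
|---|---|---|---|
| 50% vs 50% | 2%, 5%, 10% | 4.0%, 5.3%, 4.7% | 4.7%, 3.7%, 1.0% |
| 60% vs 40% | 2%, 5%, 10% | 20.7%, 38.3%, 63.0% | 3.7%, 2.0%, 3.3% |
| 70% vs 30% | 2%, 5%, 10% | 75.0%, 97.0%, 99.7% | 6.7%, 4.7%, 1.7% |

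The Monte Carlo standard error at 5% is √(0.05 × 0.95 / 300) = 1.3 percentage points.

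A separate simulation (also n = 170, Euclidean distance, DMT share about 3%, residual permutation for the adjusted test) gave 16% unadjusted against 7% adjusted at 60% vs 40%, 33% against 5% at 65% vs 35%, and 4% against 4% when balanced. The direction agrees; the sizes depend on the set-up.

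**Why a small imbalance matters.** With both factors split 50/50 overall, the correlation between exposure and DMT equals the prevalence difference: 0.60 − 0.40 = 0.20. The variance share wrongly credited to the exposure is about R² × 0.20². For R² = 5% that is 5% × 0.04 = 0.2%, on top of the 1 / 169 = 0.59% expected by chance. The spurious effect is small, but a permutation test on a many-dimensional outcome can still call it significant.

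**The case against.** The strongest reply is that the article never says adonis is run without covariates. The function accepts them, and a condensed article may leave the model formula to the full plan. This is fair. A reader might infer that the authors chose an unadjusted test, and the text does not support that; it supports only that no covariates are specified. Linear regression does not take a distance matrix as its outcome, so leaving beta-diversity out of that sentence may simply reflect the method. Alpha-diversity and abundances also begin with covariate-free rank tests. The difference is only that they have a named adjusted follow-up.

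Three other places state an intent to adjust or to model jointly, but none closes the gap. Section 2.1 gives a general aim. Action C in the Figure 2 legend describes the integrated model. The penalised models of 2.4.5 h do not take a UniFrac distance matrix as outcome, and no ordination step for this is described. The multiplicity correction in 2.4.5 g does not remove confounding.

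A reader might also infer that any exposure unevenly spread over DMT, diet, age or sex will produce false associations. It would not: the covariate must also shape the community, and the article gives no figure for either link. The simulations use Euclidean distance and a binary DMT, so they show a mechanism and do not measure this study.

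**Conclusion.** The point holds as a gap in specification that should be closed. Section 2.4.5 f attaches correction for DMT type and diet to two of the three microbiota outcomes and to no analysis of composition, although section 2.1 places all three under the same framework. Followed as written, the adonis result is open to confounding by a factor that the plan itself corrects for elsewhere.

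The size is not known. Under the assumed 60% vs 40% split, with DMT explaining 2% to 10% of community variance, false positives were 21% to 63% instead of 5%. With balanced treatment they stayed at 4% to 5%. The figures rest on the assumed imbalance, variance share, distance and dimension, and are not forecasts for this trial.

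Two further readings go too far. Section 2.4.5 f does not name age, sex or BMI; its list is introduced as partial, and those variables appear only in the wider framework of section 2.1. Nor should MEDI-LITE and DII enter every adonis model: diet is itself an exposure here, and conditioning on those scores when a dietary variable is under test would over-adjust. DMT type is the firmest part of the point. Sensitivity of adonis to unequal within-group spread is a reason for a supporting check and not an error in the article.

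**What to change.** Add to section 2.4.5 f that:

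- the adonis model for each exposure will include DMT type and the other confounders used in the adjusted linear models, omitting MEDI-LITE and DII when the exposure tested is dietary;
- the exposure will be tested by its marginal term, so that the order of terms does not matter;
- this adjusted result is the beta-diversity association to be reported, with a test of homogeneity of dispersion beside it as a supporting check.

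If a covariate-free adonis is also kept, label it descriptive.

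DMT and dietary data are already collected and the same function takes the longer formula, so neither design nor sample size changes. The cost is a few degrees of freedom and a little more analysis work.
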